## Abstract

**Background**: The World Health Organisation (WHO) included silver diamine fluoride (SDF) in the WHO Model List of Essential Medicines for the management of early childhood caries. SDF is typically available as a 38% aqueous solution, which is watery to apply. A 38% SDF gel has recently been developed, but its caries-arrest effectiveness remains unsubstantiated. The objective of this study is to determine whether the efficacy of a 38% SDF gel is non-inferior to a 38% SDF solution in arresting early childhood caries. **Methods**: This is a 30-month, randomised, active-controlled, parallel-group non-inferiority pragmatic clinical trial with two arms. The hypothesis is that the 38% SDF gel is not worse than the 38% SDF solution by a non-inferiority margin of 10% caries-arrest rate when applied semi-annually to preschool children. This trial will recruit 630 3-year-old kindergarten children through block randomisation to receive either an application of SDF gel or SDF solution on cavitated carious lesions in their primary teeth every 6 months. The primary outcome is the proportion of soft (active) carious tooth surfaces that turn hard (arrested) at the 30-month follow-up. The same calibrated dentist will conduct 6-monthly dental examinations in the kindergartens to assess the status of carious lesions over 30 months. The examiner, the children, and parents will be blinded to treatments. The parents will be surveyed on their child’s oral health-related behaviours and socioeconomic background to allow adjustment for effect modification. **Results:** If the anticipated results are obtained, clinicians can use the 38% SDF gel as an alternative of the 38% SDF solution in arresting early childhood caries. **Conclusions:** As SDF gel is cost-effective, non-invasive, and non-aerosol-generating, it can be widely recommended for caries control. **Trial registration:** ClinicalTrials.gov NCT06241261. Registered on 7 February 2024.

## 1. Introduction

### 1.1. Early Childhood Caries

Early childhood caries (ECC) is the single most common chronic childhood disease worldwide, and its high prevalence is a public health concern. The Global Burden of Disease study (2015) found that untreated ECC affected 573 million children worldwide [1]. In the United States, nearly half of all children had ECC before entering kindergarten [2], and the ECC prevalence could be as high as 98% in some parts of Canada [3]. Due to the increasing global prevalence of ECC among children aged 2–5 years, the FDI World Dental Federation has made this age group a priority [4].

ECC has adverse consequences for children’s health. Untreated dental carious lesions progress and cause local infection which can spread systemically. However, many morbid events related to ECC likely go unreported. Children with ECC are more likely to experience severe caries in adulthood and develop persistent dental fear [5,6]. In both developed and developing countries, ECC is often the main reason for school absences and tooth pain, which has an impact on children’s school performance [7,8]. ECC management is critical to the well-being of children. Traditional restorative methods for preventing and treating ECC are not widely available or affordable in Hong Kong and many countries or regions. Moreover, alternative treatments sometimes need to be administered in hospitals under general anaesthesia, which is extraordinarily costly and may exposes children to unnecessary risks [9]. The FDI Oral Health Atlas reported that millions of children in different parts of the world suffer from untreated ECC, which affects their health, well-being, and development [10]. Considering the significant impact of untreated ECC, it is urgent to develop effective and accessible treatment options.

### 1.2. Silver Diamine Fluoride

Silver diamine fluoride (SDF) is effective in managing ECC. SDF is an effective, efficient and equitable agent that can be adopted to control dental caries [11]. It is now the standard oral care for dental caries in the United States and some countries [12]. SDF therapy is safe, simple, painless, and inexpensive [13]. Treatments can be provided in kindergartens without complicated procedure or expensive equipment [14]. In 2021, the World Health Organisation (WHO) added SDF to the WHO Model List of Essential Medicines [15]. This list represents the most efficacious, safe, and cost-effective medicines for priority conditions.

SDF is currently available as a non-viscous 38% solution [16]. However, SDF solution is not easy to apply and can be easily diluted or washed away by saliva. Moreover, the aqueous solution can easily spill and stain the child’s lips and face. To solve the problem, a 38% SDF gel has recently been developed and can be applied topically. An in vitro qualitative study reported that the 38% SDF gel could penetrate and occlude dentinal tubules, which is necessary for its clinical effectiveness [17]. The gel can be applied quickly and precisely to the carious lesions with less difficulty. To date, there have been no clinical trials that have tested the effectiveness of SDF gel in arresting dental caries, nor have any studies comparatively analysed the efficacy of SDF solution and gel. In theory, the SDF gel should be comparable to the SDF solution in arresting ECC. A well-designed clinical trial is essential to verify that SDF gel is non-inferior to SDF solution in arresting dental caries. Additionally, parental satisfaction, children’s compliance, and any potential adverse effects of the two SDF therapies have also not been investigated. The findings of this study will provide clinical evidence to dental professionals for the adoption of SDF gel in managing ECC.

### 1.3. Objective

The objective of this study is to determine whether the efficacy of a 38% SDF gel is non-inferior to a 38% SDF solution in arresting early childhood caries.

### 1.4. Hypothesis

The hypothesis is that the 38% SDF gel is not worse than the 38% SDF solution by a non-inferiority margin of 10% caries arrest rate when applied semi-annually among preschool children.

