### 2.13. Sample Size and Power Calculation

In our previous clinical trial, the proportion of active carious surfaces that became arrested after the biannual application of 38% SDF solution over 24 months was 76.5% [25]. We set the non-inferiority margin at 7.65% (which corresponds to 10% of the caries arrest rate observed with the SDF solution). This non-inferiority margin represents a difference between the intervention products that we consider to be clinically insignificant. The estimated sample size is based on the lower limit of the two-sided 95% confidence interval for the difference being set above the non-inferiority margin (−7.65%) and the statistical power of the study being set at 90% (β = 0.10) by the Sealed Envelope Power (sample size) calculators [26].

This non-inferiority trial requires 1292 active-caries tooth surfaces at the 30-month follow-up assessment. We have accounted for the fact that each child may present with multiple carious tooth surfaces, with an estimated mean of 4.75 active-carious surfaces per child and an intraclass correlation (ICC) of 0.227, based on our previous study findings [25]. Furthermore, we have estimated a 30-month dropout rate of 20% and an ECC prevalence of 38% among 3-year-old children, according to the available epidemiological data [27]. Therefore, we will screen approximately 3000 3-year-old children to recruit at least 630 children with ECC, with 315 children assigned to each of the two SDF intervention groups.

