### 2.15. Statistical Analysis

Data analysis will be conducted using SPSS 24.0 software (SPSS Inc., Chicago, IL, USA). Intra-examiner agreement for caries diagnosis will be evaluated using Cohen’s Kappa statistics. Non-inferiority of the SDF gel group compared with the SDF solution group (control, caries arresting rate 76.5%) will be accepted if the lower limits of the 95% two-sided CI of the difference in the caries-arresting rate is greater than the non-inferiority margin (7.65%). This test for non-inferiority will only be performed for the primary endpoint, which is the proportion of the soft (active) carious tooth lesion surfaces that turn hard (arrested) at the 30-month follow-up. An intention-to-treat approach is planned to utilise all available data from all originally recruited children.

At subject level, chi-square tests will be used to compare proportions of arrested carious surfaces between groups during the follow-ups. These statistical tests will also be applied to analyse the incidence of new carious surfaces and dropout rates between groups during the follow-ups. Independent sample t-tests will be employed to investigate the differences in the mean values of continuous outcome measures, including the number of newly developed carious surfaces, dmfs scores, and non-vital/hypermobile teeth. Descriptive analyses will be used to report the proportions of adverse effects, as well as the levels of child and parental acceptance for each intervention. The McNemar test will be used to compare the changes in oral-health-related behaviours and children’s cooperation between different treatment groups.

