However, direct comparative evidence on the caries-arresting capacity and clinical efficacy of SDF gel versus the traditional SDF solution is limited. To address this evidence gap, this randomised controlled trial will employ a non-inferiority design to evaluate whether the SDF gel formulation is at least as effective as the standard SDF solution in arresting dental caries. We selected a 10% non-inferiority margin based on the existing literature and practical considerations in paediatric dentistry [33]. This margin allows us to assess clinical relevance while accommodating the challenges associated with sample size in the community. Given that this clinical trial requires the screening of approximately 3000 preschool children, the chosen margin strikes a balance between ensuring meaningful clinical outcomes and maintaining the feasibility of the trial. Furthermore, SDF gel may potentially offer additional benefits, such as improving application precision, reducing soft tissue staining, and enhancing patients’ acceptability. This study has large sample size which will provide adequate statistical power to detect any non-inferiority of the SDF gel compared to the SDF solution. Demonstrating the non-inferiority of SDF gel could support its clinical use, especially for paediatric patients among whom the precisely application of SDF therapies and extended contact time of the agents are prioritised. SDF gel also retains other advantages of SDF, such as affordability, accessibility, minimal invasiveness, and non-aerosol generation, making it an attractive option for public-health-oriented caries prevention and management strategies.

Overall, this study aims to provide robust clinical evidence on the effectiveness of 38% SDF gel in managing ECC. Confirming its non-inferiority to traditional SDF solution would promote its adoption, especially in public health contexts focused on paediatric oral care. The SDF gel’s affordability, ease of use, and minimal invasiveness offer a promising tool for advancing caries prevention strategies and improving children’s oral health worldwide.

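### The abstract, hypothesis and discussion give an unqualified 10% non-inferiority margin, while the sample size and decision rule use 7.65 percentage points, and the decision rule drops the minus sign

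*Protocol article*

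**What the plan says.** The margin appears in five places in the protocol article.

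- **Abstract:** the gel is "not worse than the 38% SDF solution by a non-inferiority margin of 10% caries-arrest rate".
- **1.4 Hypothesis:** the same statement, "not worse than the 38% SDF solution by a non-inferiority margin of 10% caries arrest rate".
- **2.13 Sample Size and Power Calculation:** "We set the non-inferiority margin at 7.65% (which corresponds to 10% of the caries arrest rate observed with the SDF solution". The rate is the team's earlier result, "after the biannual application of 38% SDF solution over 24 months was 76.5" per cent. The criterion is the "lower limit of the two-sided 95% confidence interval for the difference being set above the non-inferiority margin (−7.65" per cent), with the sign shown.
- **2.15 Statistical Analysis:** non-inferiority is accepted if the lower limit of the two-sided 95% interval for "the difference in the caries-arresting rate is greater than the non-inferiority margin (7.65" per cent). Here the sign is missing.
- **3 Discussion:** "We selected a 10% non-inferiority margin based on the existing literature and practical considerations in paediatric dentistry". The 10% is then defended on clinical relevance and feasibility, and 7.65 is not mentioned.

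**The concern.** In a non-inferiority trial the margin is the threshold that decides the verdict, and section 2.15 limits the non-inferiority test to the single primary endpoint. The outcome is itself a percentage. A margin of 10% on the arrest rate, with no word such as relative, is therefore naturally taken as 10 percentage points. A reader of the abstract, hypothesis or discussion would judge the result against -10, while a reader of the methods would judge it against -7.65. Some plausible results pass one threshold and fail the other.

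The missing sign in section 2.15 is a second fault in the same rule. Read literally, the lower limit would have to exceed +7.65 points, which is a demand for substantial superiority.

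**Working it through.** **Inputs, all from section 2.13:** arrest rate 76.5% (taken as equal in both arms); two-sided 95% interval, so z = 1.960; power 90%, so z = 1.2816; 4.75 surfaces per child; ICC 0.227; dropout 20%; 630 children allocated equally.

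**1. Reproduce the plan's size with a margin of 7.65 points.**
- Surfaces per arm = (1.960 + 1.2816)² × 2 × 0.765 × 0.235 / 0.0765² = 10.507 × 0.35955 / 0.005852 = 645.6, rounded up to 646. The total is 1292, as stated.
- Design effect = 1 + (4.75 − 1) × 0.227 = 1.85125.
- Children = 1292 × 1.85125 / 4.75 = 503.5. Dividing by 0.80 gives 629.4, rounded up to 630, as stated.

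**2. Repeat with a margin of 10 points.**
- Surfaces per arm = 10.507 × 0.35955 / 0.01 = 377.8, rounded up to 378. The total is 756.
- Children = 756 × 1.85125 / 4.75 = 294.6. Dividing by 0.80 gives 368.3, so 369, or 370 for equal arms.

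Of the two margins, only 7.65 points yields the published figures.

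**3. Range of results on which the two thresholds disagree.**
- Effective surfaces after dropout = 630 × 0.80 × 4.75 / 1.85125 = 1293.2, or 646.6 per arm.
- SE with equal rates = √(0.35955 / 646.6) = 2.36 points, so the half-width is 1.96 × 2.36 = 4.62 points.
- Lowest observed difference that passes at -7.65: −7.65 + 4.62 = −3.03.
- Lowest observed difference that passes at -10: −10 + 4.62 = −5.38.

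Results between about -5.4 and -3.0 points pass at -10 and fail at -7.65. If the SE is taken from the unequal rates at each limit, the half-widths are about 4.78 and 4.71. The limits then move to −10 + 4.78 = −5.22 and −7.65 + 4.71 = −2.94, which is nearly the same gap. As an example, an observed difference of -4.0 points has a 95% interval of about -8.7 to +0.7.

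**4. Chance of passing when the gel is truly 7.65 points worse.**
- The rates are 76.5% and 68.85%. SE = √((0.765 × 0.235 + 0.6885 × 0.3115) / 646.6) = √(0.39424 / 646.6) = 2.47 points.
- Against -10: Φ((10 − 7.65) / 2.47 − 1.96) = Φ(−1.008) = 0.157.
- Against -7.65: Φ(−1.96) = 0.025.

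**5. Power at the planned size if the arms are truly equal.**
- At 7.65 points: Φ(7.65 / 2.358 − 1.96) = 90.0%.
- At 10 points: Φ(10 / 2.358 − 1.96) = 98.9%.

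**The case against.** The strongest reply is that the article reconciles its own figures. Section 2.13 says in terms that 7.65 is 10% of the earlier 76.5%, and the loose wording of the abstract and hypothesis is compatible with that. Section 2.15, the only statement of the decision rule, uses 7.65 and places 76.5% beside it. No calculation uses 10 points. Most of this stands: the margin in use can be identified, and it is 7.65 points.

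It does not remove the fault. The hypothesis carries no qualifier, and the discussion presents 10% as the selected margin with its own rationale and no reference to 7.65. The section that should settle the matter prints the figure with the wrong sign.

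A reader might go further in two directions that the document does not support.

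- **Two competing margins, so that the threshold could be chosen after the data and error control is lost.** A published rule fixes 7.65, and a move to 10 would be a visible departure from it.
- **A margin that floats as 10% of this trial's own control rate, with a loss of power if that rate is low.** The rate in section 2.13 is the one observed in the earlier trial, and nothing says the margin is recalculated. Any power figure for a lower control rate would rest on an assumed rate, not on the protocol.

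**Conclusion.** The point holds as an inconsistency in how the decision threshold is stated. It is not a flaw in the design. The sample size and decision rule share one margin, 7.65 points, confirmed by exact reproduction of 1292 surfaces and 630 children. The abstract, hypothesis and discussion state it in a form that reads as 10 points.

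The size of the problem is conditional on the 10% being read as absolute and used in place of the rule in section 2.15. The two statements then disagree for observed differences of about -5.4 to -3.0 points, and a true deficit of 7.65 points would pass in about 16% of trials instead of 2.5%. If the 10% is read as relative to 76.5%, there is no numerical difference. These figures rest on the plan's own control rate, cluster size, ICC and dropout, and on the normal approximation.

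The missing minus sign in section 2.15 is a plain wording error; section 2.13 shows the intended sign.

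**What to change.** In the abstract, section 1.4, section 2.15 and the discussion, state the same margin: an absolute difference in arrest rate, gel minus solution, of -7.65 percentage points. Mention 10% only to explain that 7.65 is 10% of the assumed 76.5%. Restore the minus sign in section 2.15.

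Add one sentence saying that the margin stays at -7.65 points whatever control rate is observed. This is worth stating because the 76.5% is a 24-month figure and the endpoint is at 30 months, so the control rate may differ. For illustration, 10% relative would be 6.0 points at an assumed control rate of 60% and 9.0 points at 90%.

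The cost is a wording amendment, best made before outcome data are seen. The 630 children were computed for 7.65 points, so neither the size nor the conduct of the trial changes.

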### 1.5. Outcome Measures

The primary outcome is the proportion of soft (active) carious tooth surfaces that turn hard (arrested) at the 30-month follow-up. The secondary outcomes are parental satisfaction, children’s compliance, and adverse effects of the SDF therapy.

## 2. Methods/Design

### 2.1. Trial Design

This is a 30-month single-centre randomised, active-controlled, parallel-group non-inferiority pragmatic clinical trial with two arms. It follows the Standard Protocol Items: Recommendations for Interventional Trials (SPIRIT) 2013 Statement [18]. Figure 1 shows the trial’s schedule of enrolment, interventions, and assessments. and Supplementary Materials present the SPIRIT 2013 Checklist: Recommended items to address in a clinical trial protocol and related documents.

### 2.2. Ethics Approval and Trial Registration

The trial was approved by the Institutional Review Board of the University of Hong Kong/Hospital Authority Hong Kong West Cluster (UW23-064) on 22 February 2023 and registered in ClinicalTrials.gov (NCT06241261) on 7 February 2024 and Chinese Clinical Trial Registry (ChiCTR2400089113) on 2 September 2024. The trial has been recruiting the first participating child since 1 March 2024 and is expected to complete the recruitment by 31 December 2024.

### 2.3. Setting and Location

This trial will be conducted in kindergartens. The investigators will invite kindergartens which provide outreach dental services. Children aged 3 to 4 years old attending the first year of the recruited kindergarten will be invited to join the trial. An invitation letter explaining the purpose and procedures of the study will be distributed to parents or legal guardians of the children. Kindergarten teachers will collect written informed consent from the parents or guardians prior to the enrolment and pass the consent to the investigators.

### 2.4. Participants

The participants will be children aged 3 to 4 years old who:

(1) are currently attending their first year of kindergarten;

(2) are generally healthy as reported by their parents;

(3) have at least one active carious lesion presented in their primary dentition;

(4) have written informed consents from their parents or legal guardians.

Children will be excluded if they:

(1) are uncooperative impeding the oral examination and/or fluoride therapy;

(2) suffer from major systemic diseases such as porphyria;

(3) are under long-term usage of medications like antiepileptics;

(4) have teeth with dental pulp exposure.

### 2.5. Questionnaire Survey

A parental questionnaire will be administered at the baseline and at the 18-month and 30-month follow-ups [19]. The baseline questionnaire will collect information about children’s oral-health-related behaviour (oral hygiene habits, the use of fluoride agent, parent-assisted tooth-brushing, dental visit behaviour, and snacking habits), and family background information (parental educational level, total family income and family status). The follow-up questionnaires will reassess the children’s oral health-related behaviour and measure parental satisfaction towards their children’s oral health status and appearance by five-point Likert scale. Parents will also be asked to report any potential complications or adverse events experienced by their child after the SDF application, such as tooth pain or gingival irritation.

### 2.6. Clinical Examinations

A trained examiner will perform oral examinations using a WHO periodontal ball-end probe (Otto Leibinger, Mühlheim, Germany) and a front-surface dental mirror with LED illumination (Kudos Crowns Limited, Hong Kong SAR, China) [20]. Tooth status including decayed, missing, and filled tooth surfaces (dmfs) scores, tooth mobility, and discolouration will be recorded. Dental caries will be diagnosed at the cavitation level using visual–tactile assessment. The WHO periodontal ball-end probe will be used to gently explore the centre of suspected carious lesions and carefully avoid any tooth damage. All tooth surfaces will be examined, including the five surfaces of posterior teeth (buccal, lingual, mesial, distal, and occlusal) and the four surfaces of anterior teeth (buccal, lingual, mesial, and distal).

A carious lesion will be classified as active if it is soft during gentle probing. In contrast, if a carious lesion is hard upon probing will be classified as arrested. The assessment of carious lesions is consistent with our previous study [21]. Radiographic imaging will not be performed in this school-based study setting. The examiner will also assess the child’s oral hygiene status using the Visible Plaque Index (VPI) by examining the buccal and lingual surfaces of six index teeth (55, 51, 63, 71, 75, and 83).

Additionally, the presence of visible dental plaque on any existing carious lesions will also be recorded. Intra-examiner agreement will be conducted on 10% of the children who are also the participants of this study at each examination stage to ensure consistency and reliability of the clinical assessments.

